#### Secondary Objectives

• To describe the profile of detectable autoantibodies over a 48-weeks follow-up in patients with cancer treated with ICIs, regardless of whether they develop irAEs• To compare irAE-free survival among patients positive for autoantibodies before ICI initiation, patients positive for autoantibodies after ICI initiation and patients negative for autoantibodies throughout follow-up• To analyze cancer-related survival in patients treated with ICIs who develop irAEs and compare it with that in patients who do not develop irAEs• To investigate the potential early appearance and/or aggregation of autoantibodies over time up to the time of irAEs diagnosis.

This study protocol corresponds to the first phase of the AUTENTIC project, which will be followed by an external validation of a predictive model of irAEs with prospective data in an independent cohort of patients.

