### Endpoints

The primary endpoint of the study will be the proportion of patients developing at least an irAE at week 48 after the initiation of ICI therapy. An irAE was defined as any symptom, sign, syndrome, or disease caused by an immune-activating mechanism during the administration of an ICI once other causes such as an infectious disease or tumor progression have been ruled out.

Key secondary endpoints will be irAE-free survival, progression-free survival, cancer-related survival and overall survival. Other secondary outcomes will be proportion of ICI withdrawal due to the occurrence of irAEs, time to autoantibody appearance and number of positive autoantibodies included in the panel at week 48 after the initiation of ICI therapy.

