### Setting and Duration

The current study will consecutively enroll patients diagnosed with different types and stages of solid organ malignant tumors who are candidates for treatment with ICIs. In the setting of outpatient clinics, patients will be recruited by the medical oncologists responsible for their care in one of the participating hospitals. Recruitment will continue until the desired sample size is reached (see “*Study size calculation*” section). The autoantibody panel under study will be performed when the whole cohort reaches week 48 of follow-up from the time of inclusion, which will coincide with the ICI initiation date. Patients lost to follow-up will be censored at the time of their last follow-up.

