Data related to the tumour:• Tumour type• Date of diagnosis• PD-L1 expression in tumour cells (%)• Date of initiation of ICI therapy• Dates of ICI administration• Date of progression• Date of death• Progression-free survival, defined as time from start of ICI therapy to tumor progression, death or last day of follow-up• Overall survival, defined as time from start of ICI therapy to death or the last day of follow-up• Cause of death: cancer-related, non-cancer-related, ICI-associated toxicity (immune-related, non-immune-related adverse event, infection or other).

Data related to treatment received before ICI initiation:• Nonsteroidal anti-inflammatory drugs• Glucocorticoids• Other immunomodulatory drugs: e.g., colchicine, hydroxychloroquine, mesalazine, or sulfasalazine• Oral anticoagulants (acenocoumarol, low-molecular-weight heparin, direct oral anticoagulants).

Data related to ICI:• Type: anti-CTLA4 (ipilimumab), anti-PD1 (nivolumab and pembrolizumab), anti-PD-L1 (atezolizumab, avelumab, and durvalumab)• Monotherapy or combination therapy (description)• Adjuvant or palliative therapy, and if palliative, line of therapy (first line, second line, other).

Laboratory data:

Obtained from blood samples for care and research purposes:• Glomerular filtration rate (ml/min/m^2^), levels of glucose (mg/dl), bilirubin (mg/dl), alanine aminotransferase, aspartate aminotransferase, gamma-glutamyltransferase (U/L), and thyroid stimulating hormone (μUI/mL).• Prothrombin time (percentage) or international normalized ratio (INR)• Complete cell count: haemoglobin (g/dl), white blood cells (/µL), differential white blood cell count of neutrophils, lymphocytes, monocytes, and eosinophils (/μL) and platelets (/μL)• Lipid profile: levels of cholesterol, triglycerides, and high- and low-density lipoprotein cholesterol (mg/dl).

Obtained from blood samples only for research purposes:• 25-hydroxycholecalciferol (ng/ml) at weeks 0, 24 and 48.• Levels of the autoantibodies under study (i.e., ANAs, RF and ANCAs) in ordinary samples according to study schedules (Figures 1, 2) and extraordinary samples.

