Survival will be assessed using a Kaplan-Meier analysis and compared between groups using the log-rank Mantel-Cox test. A subgroup analysis according to tumour type and extent of cancer (local, advanced, and metastatic disease) will be performed to assess survival outcomes*.* A multivariate analysis using logistic regression and Cox regression will be performed to detect factors associated with the occurrence of irAEs. Applying a manual backward stepwise procedure, a multivariate model will be constructed from variables that either have a p-value of less than 0.10 in the univariate analysis or are considered relevant to the dependent variable on the basis of previous studies (e.g., sex and age of patients, type of ICI). Variables not reaching statistical significance will be dropped from the final predictive model. The sensitivity, specificity, positive predictive value, negative predictive value, and probability ratios with their corresponding 95% confidence intervals of the model will be calculated. The diagnostic accuracy of the predictive model inferred from the logistic regression model will be described with the area under the receiver operating characteristic curve.

Two-sided hypothesis tests will be performed, and the significance level will be set at 5%. The statistical analysis will be conducted using IBM SPSS Statistics software version 27.0 (Chicago, IL).

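### Comparing cancer-related survival by whether an irAE ever develops, with log-rank from ICI start, builds in immortal time that favours the irAE group (should-fix)

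*Protocol article*

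**What the plan says.** Under Secondary Objectives, the protocol article plans "To analyze cancer-related survival in patients treated with ICIs who develop irAEs and compare it with that in patients who do not develop irAEs". Endpoints lists cancer-related survival, with overall and progression-free survival, among the key secondary endpoints. The Summary at the end of the Introduction describes the aim as the impact of irAEs on cancer-related survival.

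The method is in Sample Size Calculation and Statistical Analysis: "Survival will be assessed using a Kaplan-Meier analysis and compared between groups using the log-rank Mantel-Cox test". Cox regression appears there for a different purpose: a "multivariate analysis using logistic regression and Cox regression will be performed to detect factors associated with the occurrence of irAEs". In that model the irAE is the outcome, not the exposure.

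The time origin is given in Variables: "Overall survival, defined as time from start of ICI therapy to death or the last day of follow-up" and "Progression-free survival, defined as time from start of ICI therapy to tumor progression, death or last day of follow-up". Setting and Duration adds that the panel is run at "week 48 of follow-up from the time of inclusion, which will coincide with the ICI initiation date". Cancer-related survival has no definition of its own.

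An irAE is defined in Endpoints as an event "caused by an immune-activating mechanism during the administration of an ICI", and Variables records its date of diagnosis. Management of Potential Bias discusses selection of patients with autoimmune disease and detection bias, but not the timing of irAEs.

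**The concern.** The clock starts at ICI initiation, but the groups are formed by something that may happen at any time in the next 48 weeks. To enter the irAE group a patient must first live long enough to have an irAE. The weeks before onset are death-free by construction in that group, yet the log-rank test counts them as time at risk with an irAE. Deaths that come before any irAE all go to the other group.

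Both effects push the same way. If irAEs have no bearing on death, the comparison will tend to show them as protective. If they truly raise mortality, the bias will shrink or hide the harm. Counting irAEs only while ICI is being given works in the same direction, since patients who stop treatment early have less time to qualify.

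What is at stake is the interpretation of a key secondary endpoint on the balance between toxicity and benefit.

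**Working it through.** **The plan's own figure.** The article gives no figure for the survival comparison, only the sample size. 70 cases / 0.25 = 280 patients, and 280 × 1.05 = 294, so the stated total is reproduced. The check below uses the 280 evaluable patients.

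**Inputs from the article.** 25% of patients with an irAE, 48 weeks of follow-up, two-sided 5% test.

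**Assumptions, because the article gives no figures.** Mortality by week 48 of 10% to 60% with a constant hazard. Three onset patterns: early (a susceptible fraction, latent median 8 weeks), intermediate (same, latent median 12 weeks) and constant hazard. Each is calibrated to about 25% observed irAEs. An irAE has no effect on death.

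**Hand check at 30% mortality, constant onset hazard.**
- Death hazard: λ = −ln(0.70)/48 = 0.00743 per week.
- Onset hazard h solves h/(h+λ) × [1 − exp(−48(h+λ))] = 0.25, giving h = 0.00726 per week.
- Alive at week 48 with an irAE: 0.70 × [1 − exp(−48 × 0.00726)] = 0.70 × 0.294 = 0.206.
- Survival in the irAE group: 0.206/0.25 = 82.4%.
- Survival in the no-irAE group: (0.70 − 0.206)/0.75 = 65.9%.

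The gap of 16.5 percentage points arises although death is unrelated to irAE. For early onset the onset rate is r = ln(2)/8 = 0.0866 per week:
- Share of susceptible patients with an observed irAE: r/(r+λ) × [1 − exp(−48(r+λ))] = 0.911, so the susceptible fraction is 0.25/0.911 = 0.274.
- irAE group: 0.70 × 0.274 × [1 − exp(−48r)]/0.25 = 75.6%.
- No-irAE group: 68.1%.

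**Simulation.** 2,000 cohorts of 280 per scenario (400 for the time-dependent test). The ever/never hazard ratio comes from one Cox fit to 20,000 simulated patients, so its second decimal is uncertain, most of all at 10% mortality. False protective means p < 0.05 in favour of irAE; the nominal rate is 2.5%.

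| 48-week mortality | Onset | Ever/never HR | 48-week survival, irAE v none | False protective | Time-dependent: HR, two-sided rejection | Week-12 landmark: HR, two-sided rejection |
|---|---|---|---|---|---|---|
| 10% | early | 0.62 | 92.1% v 89.3% | 6.7% | 1.02, 3.7% | 1.01, 4.1% |
| 10% | intermediate | 0.59 | 92.7% v 89.1% | 11.6% | 1.03, 3.7% | 1.02, 4.8% |
| 10% | constant | 0.49 | 94.7% v 88.5% | 29.5% | 0.97, 4.3% | 1.00, 4.1% |
| 30% | early | 0.69 | 75.7% v 68.1% | 23.7% | 0.99, 3.7% | 1.01, 4.9% |
| 30% | intermediate | 0.64 | 77.4% v 67.6% | 37.3% | 1.00, 7.0% | 1.03, 5.4% |
| 30% | constant | 0.41 | 82.4% v 65.9% | 81.2% | 0.99, 3.7% | 1.02, 4.4% |
| 60% | early | 0.68 | 48.3% v 37.3% | 53.7% | 1.00, 3.7% | 1.01, 4.9% |
| 60% | intermediate | 0.60 | 51.3% v 36.2% | 78.8% | 1.01, 6.5% | 1.01, 5.2% |
| 60% | constant | 0.45 | 58.9% v 33.6% | 99.8% | 1.00, 4.5% | 1.02, 5.5% |

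Over the full grid (10% to 60% in steps of 10) the ever/never hazard ratio is 0.41 to 0.69. The time-dependent analysis gives 0.97 to 1.04 with 3.7% to 8.3% rejection (Monte Carlo standard error about 1.1 points). The landmark gives 1.00 to 1.03 with 4.1% to 5.9%. A second simulation under the same null at 10% to 50% mortality gave hazard ratios of about 0.43 to 0.70 and false protective findings in about 11% to 98% of cohorts.

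**The case against.** **Two links are inferred.** ICI start is stated as origin for overall and progression-free survival only, and the log-rank sentence is general and serves other comparisons too. Both points are fair. Still, inclusion coincides with ICI start, no other origin is offered, and log-rank is the only between-group survival method given for an objective that asks for exactly such a comparison. A fuller plan may exist, but the article does not leave the method open: it names one that does not suit this objective.

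**The size is uncertain.** This stands. Tumours of any stage are eligible and adjuvant therapy is recorded, so low mortality is plausible. With 10% mortality and early onset the excess of false findings is modest.

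A reader might also infer more than the article supports:

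- *That every early death falls in the no-irAE group.* It does not. A patient with an early irAE who then dies early is in the irAE group. Only deaths before an irAE could occur are forced into the other.
- *That the study will report a benefit.* That is not certain: the false-positive rate varies widely, and a true harm might only be masked.
- *That the bias would confirm a survival benefit claimed in the rationale.* The Introduction cites a higher response rate with irAEs, not longer survival, and goes on to say that immunosuppression for irAEs may reduce the anti-tumour effect.
- *That toxicity deaths are a second fault.* Variables lists "Cause of death: cancer-related, non-cancer-related, ICI-associated toxicity" as separate categories, but how cancer-related survival treats them is not stated. The toxicity category also includes non-immune events and infection, which can occur in either group. The simulation does not model this, and a cause-specific analysis of cancer death would likewise not count such deaths as events.

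**Conclusion.** The concern holds for immortal time. Followed as written, the comparison by irAE status is biased in favour of the irAE group whatever the mortality and onset pattern assumed here. With no true effect the hazard ratio is about 0.4 to 0.7. False protective findings run from roughly 7% to 11% (10% mortality, early onset) to nearly all studies (high mortality, constant-hazard onset), against a nominal 2.5%. These sizes rest on assumed mortality and onset timing, constant death hazards and about 25% irAEs. The direction does not depend on the particular values. The simulation leaves out the restriction of irAEs to time on ICI.

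The grade is should-fix. One key secondary objective is affected. The primary objectives, the primary endpoint and the sample size of 294 are untouched, and no data would be lost.

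**What to change.** In Sample Size Calculation and Statistical Analysis, for this objective, replace the ever/never log-rank comparison from ICI start with:

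1. A Cox model with irAE as a time-dependent covariate: each patient is unexposed until the date of irAE diagnosis and exposed afterwards.
2. One prespecified landmark analysis (for example at week 12) among patients still alive and under follow-up at that date, grouped by irAE status then, with Kaplan-Meier and log-rank from the landmark.

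Apply the same to any comparison of progression-free and overall survival by irAE status. State the time origin of cancer-related survival, and report overall survival, already a key secondary endpoint, alongside it.

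The cost is analysis wording only: Variables already lists the dates of irAE diagnosis, progression and death, and the cause of death. The landmark analysis drops patients who die before the landmark and counts later irAEs as unexposed, which is why the time-dependent model should lead.

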### Follow-Up Methods

Once enrolled in the study, patients will be monitored following standard recommendations. In accordance with clinical practice guidelines (Schneider et al., 2021; Schneider et al., 2022), all patients will be assessed in a treatment planning visit at baseline. In this initial visit, attending physicians will take a detailed personal and family history focused on ADs, chronic infectious and organ-specific diseases, and conduct a physical examination. In addition, to guide their care, patients will undergo a baseline blood test including a complete blood count, measurement of glucose and thyroid stimulating hormone (TSH) levels and lipid profile, renal and liver function tests, coagulation tests, and serological tests for hepatitis B and C viruses and HIV.

The frequency of follow-up will depend on the treatment schedule of each specific ICI, discretion of the attending physician and occurrence of complications (irAEs, non-immune-related toxicity, infections). All patients will have direct telephone access to the investigators in order to report early symptoms potentially related to the occurrence of irAEs*.* Treatment schedules of the ICIs will be classified into every 2 or 3 weeks up to week 12; thereafter, drug administration may be spaced out to every 4 or every 6 weeks, respectively, according to the drug data sheets.

Two types of blood samples will be taken for research purposes only: ordinary samples, defined as those drawn routinely as scheduled (Figure 1 and Figure 2), and extraordinary samples, defined as those taken at the time an irAE is detected. As far as possible, ordinary blood samples will be collected at the same time as blood draws for medical purposes before the administration of each ICI dose, in accordance with the study schedules (Figures 1, 2).

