#### Ordinary Samples and Study Schedules

Prior to receiving the first dose of ICI, all patients will undergo a baseline (i.e., week 0) blood test for research purposes, at the same time as their baseline blood test for medical purposes.

For ICIs administered every 2 weeks (nivolumab, avelumab, and durvalumab), sequential blood tests will be performed per protocol at weeks 2, 6, 12, 24, 36 and 48 after ICI initiation, all of them at the same time as draws for medical purposes (Figure 1). In other words, four ordinary samples will be obtained in the first 12 weeks (i.e., at 0, 2, 6, and 12 weeks after ICI initiation). Thereafter, the ordinary blood sampling interval will be every 12 weeks up to the end of follow-up at week 48.

For ICIs or combinations of ICIs administered every 3 weeks (ipilimumab plus nivolumab, pembrolizumab, and atezolizumab), sequential blood tests will be performed at weeks 0, 3, 6, 12, 24, 36 and 48 after ICI initiation, all of them at the same time as draws for medical purposes (Figure 2). In other words, four ordinary samples will be obtained in the first 12 weeks (i.e., at 0, 3, 6, 12 weeks after ICI initiation). Thereafter, the ordinary blood sampling interval will be 12 weeks up to the end of follow-up at week 48.

In the event of a delay in the administration of an ICI dose due to any eventuality other than an irAE, the ordinary sample corresponding to that treatment cycle will not be obtained. If the delay is due to the occurrence of an irAE, then an extraordinary sample will be obtained, as per protocol (see “*Extraordinary samples*” in the next section). Once treatment resumes, the ordinary sample corresponding to that treatment cycle will be collected per protocol.

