#### Extraordinary samples

At the time an irAE is detected, an additional blood sample will be collected for tests including the autoantibody panel under study. At the discretion of the attending physician, screening for other more specific antibodies may be requested based on the clinical manifestations of the patient. For ethical and decision-making reasons, the results of these extraordinary analyses for medical purposes will be available to the attending physicians.

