### Variables

Patients included in the study will be identified by a numerical code. In this way, the data collected by researchers will not include personal information, safeguarding patient confidentiality. The transmission, processing, and dissemination of personal data from all the participating patients will be handled in accordance with Regulation (EU) 2016/679 of the European Parliament and of the Council of 27 April 2016 on the protection of natural persons regarding the processing of personal data and the free movement of such data, i.e., the General Data Protection Regulation.

Study data will be entered into an electronic database to which all participating hospitals will have centralized access, and which will comply with all data protection requirements.

Dependent variable: occurrence of irAEs.

An irAE is defined as any symptom, sign, syndrome, or disease caused by an immune-activating mechanism during the administration of an ICI once other causes such as an infectious disease or tumor progression have been ruled out.

Other descriptive variables related to irAEs:• Description of symptoms related to the irAE• Type: organ-specific or systemic (≥ 2 organs affected)• Description of the involved organ• Syndrome/disease: Sjögren’s syndrome, sarcoidosis, systemic vasculitis, systemic lupus erythematosus, etc.• Severity, according to Common Terminology Criteria for Adverse Events v. 5.0• Date of diagnosis of the irAE• Treatment used for the irAE: non-steroidal anti-inflammatory drugs, glucocorticoids, immunosuppressive drugs other than glucocorticoids• ICI dose reduction: yes/no• ICI withdrawal: yes/no; if yes: temporary/permanent.

Independent variables: the following potential predictors of irAEs will be collected and analyzed: Epidemiological data: date of birth, sex, ethnicity.

General clinical data:• Smoking and alcohol use• Comorbidities: arterial hypertension, hypercholesterolemia, diabetes mellitus, cirrhosis/liver failure, renal insufficiency, thyroid dysfunction• Chronic infections: hepatitis B, hepatitis C, HIV infection• Autoimmune diseases prior to ICI initiation• Type of previous autoimmune disease (description)• Eastern Cooperative Oncology Group performance status score• Body mass index (in kg/m^2^).

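### The early-appearance window for autoantibodies closes at irAE diagnosis, the only irAE date listed, so it cannot separate antibodies that precede toxicity from those first found during the work-up

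*Protocol article*

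**What the plan says.** Under Secondary Objectives, the protocol article plans "To investigate the potential early appearance and/or aggregation of autoantibodies over time up to the time of irAEs diagnosis". The irAE items under Variables include one event date, "Date of diagnosis of the irAE". Symptoms appear there as "Description of symptoms related to the irAE", with no date attached. The definition, given under Endpoints and again under Variables, accepts a symptom, sign, syndrome or disease as an irAE "once other causes such as an infectious disease or tumor progression have been ruled out".

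Blood is drawn on two tracks. For two-weekly ICIs, after the week 0 sample, "sequential blood tests will be performed per protocol at weeks 2, 6, 12, 24, 36 and 48 after ICI initiation". For three-weekly ICIs, "sequential blood tests will be performed at weeks 0, 3, 6, 12, 24, 36 and 48 after ICI initiation". In addition, "At the time an irAE is detected, an additional blood sample will be collected for tests including the autoantibody panel under study". Laboratory Management and Sample Circuit describes that same extra sample as taken at irAE diagnosis, so detection and diagnosis are treated as one moment.

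Follow-Up Methods gives patients telephone access "in order to report early symptoms potentially related to the occurrence of irAEs", so information about first symptoms can reach the investigators.

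**The concern.** The scientific question is one of order. The Introduction asks whether autoantibodies are a step that comes before toxicity. The Discussion reasons from autoimmune diseases in which antibodies are present before the disease shows itself. To test that, the window must close when the irAE first shows itself. A window that closes at diagnosis shows only that the antibody came before the event was labelled.

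Because attribution requires other causes to be excluded, the label can trail the first symptom. An ordinary sample drawn in between lies inside the window, and nothing in the article classes it separately. If an antibody is first positive in that sample, it may be a companion or a consequence of the toxicity, yet it can be reported as early appearance. That would favour the study's hypothesis. If an onset date is not collected, the analysis stage cannot recover it.

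**Working it through.** **Inputs from the article**

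- Ordinary draws at weeks 0, 2, 6, 12, 24, 36, 48 (two-weekly ICIs) or 0, 3, 6, 12, 24, 36, 48 (three-weekly ICIs), from Ordinary Samples and Study Schedules.
- 70 irAE cases, from Sample Size Calculation and Statistical Analysis, used only for scale. The plan's totals reproduce: 70 / 0.25 = 280, 280 - 70 = 210 non-cases, 280 x 1.05 = 294. Adding an onset date would not change them.

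**Assumed inputs**

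- Onset-to-diagnosis lag L. The article gives none; 2 to 4 weeks is the working range, with 1 and 6 weeks shown around it.
- Onset spread evenly over follow-up.

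**Formula.** An irAE with onset at week t has an ordinary draw in the gap if a sampling week lies between t and t + L. The share is the number of onset weeks for which this holds, divided by the number of onset weeks considered.

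**Onset in weeks 0-12**

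- L = 2, draws at 2, 6, 12: onset in 0-2, 4-6 or 10-12, so 6/12 = 50%.
- L = 2, draws at 3, 6, 12: onset in 1-3, 4-6 or 10-12, so 6/12 = 50%.
- L = 4, draws at 2, 6, 12: onset in 0-6 or 8-12, so 10/12 = 83%.
- L = 4, draws at 3, 6, 12: the same 10/12 = 83%.

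**Onset in a later 12-week interval between draws.** The share is L/12: 2/12 = 17% and 4/12 = 33%.

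**All irAEs diagnosed by week 48.** Onset must then fall before week 48 - L, so the week 48 draw cannot lie in the gap and only the week 24 and week 36 draws count after week 12. Both schedules give the same values.

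| Lag (weeks) | Onset weeks 0-12 | Onset after week 12 | All | Out of 70 cases |
|---|---|---|---|---|
| 1 | 3/12 = 25% | 2/35 = 6% | 5/47 = 11% | 7 |
| 2 | 6/12 = 50% | 4/34 = 12% | 10/46 = 22% | 15 |
| 4 | 10/12 = 83% | 8/32 = 25% | 18/44 = 41% | 29 |
| 6 | 12/12 = 100% | 12/30 = 40% | 24/42 = 57% | 40 |

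The later-onset column is lower than L/12 because it leaves out irAEs whose gap contains week 48. If those are kept, the overall shares are (6 + 6)/48 = 25% for 2 weeks and (10 + 12)/48 = 46% for 4 weeks.

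**What the figures count.** They count irAEs with a scheduled draw in the gap. For a given lag and onset pattern they are upper bounds on draws actually made, because an ordinary sample is not taken when a dose is delayed for a reason other than an irAE. They exclude the detection-time sample. If that sample is taken as lying within the window, every case that has one has at least one draw at or after onset inside it.

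**The case against.** Several objections have force.

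- **The article is a summary.** The full protocol or case-report form may date the first symptom. That would settle the data field, but the objective itself names diagnosis as the end of its window, and that wording would still need to change.
- **No rule classes these samples as preceding the irAE.** A reader might infer that every antibody found after onset will be counted as preceding it. The article does not say so. It sets a window and leaves the classification open, so the fault is that the window permits the misreading.
- **Lead time.** A reader might infer that every antibody lead time is overstated by the whole lag. The plan defines no lead time, and the outcome on time to autoantibody appearance names no irAE anchor. There is also an opposing error. With draws 12 weeks apart, first detection trails seroconversion by about 12/2 = 6 weeks on average under even timing, so the net direction is not fixed.
- **Other endpoints.** A reader might infer that irAE-free survival is lengthened, or that irAEs starting before week 48 but diagnosed later are lost. Endpoints gives no event date for irAE-free survival and speaks of patients developing an irAE, so neither consequence is stated.
- **The definition does not force a lag.** Excluding other causes is a condition of attribution. Where the first sign is a laboratory abnormality, detection and onset may coincide, and telephone access may shorten the delay.
- **Onset dates can be biased too.** Physicians see the extraordinary-sample results taken for medical purposes, so an onset date assigned afterwards could be coloured by them.

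The last four objections limit the point to the early-appearance objective and shape the remedy. They do not make diagnosis a suitable anchor for a question about what comes before manifestation.

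**Conclusion.** The point holds for the early-appearance objective. The window ends at diagnosis, the listed variables contain no earlier irAE date, and the hypothesis concerns antibodies that precede clinical manifestations. An antibody first found between manifestation and diagnosis can therefore be read as an early marker.

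Under an assumed lag of 2 to 4 weeks and evenly spread onset, about 22% to 41% of irAEs diagnosed by week 48 (15 to 29 of 70) would have a scheduled ordinary draw in the gap. Early irAEs are the most exposed. The number of seroconversions actually misclassified cannot be derived from the article. The exposure is nil where diagnosis and first manifestation coincide, and baseline positivity is unaffected for de novo irAEs. The documents do not support extending the point to the primary endpoint or to the sample size.

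**What to change.** 1. Under Variables, add the date of the first symptom, sign or laboratory abnormality attributed to the irAE, beside the diagnosis date. Have it assigned without reference to antibody results.
2. Under Secondary Objectives, end the early-appearance window at that date. Count only samples drawn before it as preceding the irAE.
3. Report the detection-time sample separately.
4. Repeat the analysis with the diagnosis date as a sensitivity analysis.
5. For irAE-free survival, state which date is the event date and show the other as a sensitivity analysis.

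No change to the primary endpoint is required. The cost is one data field and some wording. Onset dates carry some recall error, which holding both dates allows to be examined. Fewer samples will be classed as preceding the irAE, so apparent early positivity may fall. If the full case-report form already holds an onset date, only the wording and the analysis rule need to change.
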